#### 1.2.2. Secondary Hypotheses

Participants who have higher data usage in the active VeNS group will have statistically significant changes in insomnia severity and improved quality of life after the 4-week treatment that will be maintained during the 12-week follow-up. There will be no change in insomnia and quality of life in the sham VeNS group immediately after treatment and at the post-treatment follow-up at 12-weeks.

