### 2.4. Eligibility Criteria

To obtain a homogenous sample, the inclusion criteria will be: (1) having a GAD-7 score > 10; (2) ethic Chinese, aged 18–60 years; (3) able to understand/read Chinese; (4) having an Insomnia Severity Index < 14; (5) able to provide written informed consent; (6) having Wi-Fi and Bluetooth network in iOS/Android mobile phones; (7) able to attend the face-to-face demonstration session for proper use of the MS device and return-demonstrate to research assistants in the training venue (Integrative Health Clinic, School of Nursing, The Hong Kong Polytechnic University; (8) willing to engage with the project team on a weekly basis via zoom meetings/WhatsApp/telephone to ensure compliance, proper usage of the MS device and report any technical issues; (9) not undergoing any extreme lifestyle changes that may impact on sleep quality (e.g., dietary changes/increase/decrease exercise levels) throughout the study period; (10) not taking any prescribed/over the counter anxiolytics.

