## 3. Statistical Analyses

All statistical analyses will be performed using the statistical software R for Windows (R version 4.1.0). Means and standard deviations (SD) for the continuous variables will be presented, while numbers and percentages for the categorical variables will be shown. A *p*-value < 0.05 is considered statistically significant. Sociodemographic differences between the VeNS group and the sham VeNS group will be analyzed using the chi-square test and t-test. If there are significant differences between sociodemographic factors, covariates will be considered as confounding variables in the analyses. Normality of the primary outcome (GAD-7) scores will be tested using the Shapiro–Wilk test for each combination of factor levels (group and time). A t-test will be used to test the baseline difference. Analysis of variance (ANOVA) with repeated measures will be used to test the group (between-subject factor), time (within-subject factor), and group x time interaction effects of the GAD-7 score between the VeNS group and the sham VeNS group. Post hoc comparisons between groups and time points will be conducted using a *t*-test with the Bonferroni correction. Normality of the secondary outcome scores will be tested using the Shapiro–Wilk test for each time point. For normally distributed outcomes, ANOVA with repeated measures will be used to determine whether the outcome scores are significantly different between pre-and post-test periods. For outcome scores that are normally distributed, a non-parametric Friedman test will be used to test the mean difference. A Cohen’s d effect size for each outcome will be calculated, where d = 0.2, 0.5, and 0.8, corresponding to small, medium, and large effect sizes, respectively. Participants’ total usage time will also be used to investigate the effectiveness of the VeNS on anxiety and total usage time will be used as a continuous covariate in a linear regression model for GAD-7 total score. Missing data will be managed with multiple imputation [36] by adopting the last observation carried forward (LOCF) method.

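### Secondary outcomes (ISI and SF-36) are assigned only a pre-versus-post test, with no between-arm test named, and the Friedman fallback cannot compare arms

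*Protocol article*

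**What the plan says.** Section 3 (Statistical Analyses) treats the primary and secondary outcomes differently.

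- **GAD-7.** Normality "will be tested using the Shapiro–Wilk test for each combination of factor levels (group and time"). The repeated-measures ANOVA covers group, time and "group x time interaction effects of the GAD-7 score between the VeNS group and the sham VeNS group". The next sentence reads: "Post hoc comparisons between groups and time points will be conducted using a *t*-test with the Bonferroni correction".
- **Secondary outcomes.** The normality check is made without regard to arm: "Normality of the secondary outcome scores will be tested using the Shapiro–Wilk test for each time point". Where a score passes that check, the article's plan is that "ANOVA with repeated measures will be used to determine whether the outcome scores are significantly different between pre-and post-test periods". The sentence after that reads: "For outcome scores that are normally distributed, a non-parametric Friedman test will be used to test the mean difference".

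Section 1.2.2 (Secondary Hypotheses) expects change in insomnia and quality of life among higher users in the active arm. For the other arm it states: "There will be no change in insomnia and quality of life in the sham VeNS group immediately after treatment", and it extends this to the 12-week follow-up.

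**The concern.** The secondary hypotheses set the active arm against sham, but the stated test asks only whether scores move over time. A pre-post test cannot separate a device effect from placebo response, natural improvement or regression to the mean; the sham arm exists to make that separation. Followed as written, the plan could report an improvement shared by both arms as a benefit of VeNS on insomnia or quality of life.

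The fallback has two faults. As printed, the ANOVA and the Friedman test are both assigned to normally distributed scores, and no test is named for the rest. If the missing 'not' is restored, the Friedman test still ranks repeated measurements within each person. It has no between-arm factor, and it does not test a difference in means.

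The sham hypothesis of no change has a related problem: a non-significant pre-post result in a small arm does not show that nothing changed.

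**Working it through.** **1. The plan's own sample size (Section 2.2).** Inputs: d = 1.3, power 99%, alpha 0.05, attrition 30%. Two-sided testing is assumed, since sidedness is not stated.

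- Two-sample t-test, noncentrality d x sqrt(n/2). With n = 23 per arm: 1.3 x sqrt(11.5) = 4.41, power 0.9906. With n = 22: power 0.9878.
- So 23 per arm are needed. 23 / 0.70 = 32.9, rounded up to 33 per arm and 66 in total.

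The stated figure reproduces. Numbers for the next step are therefore 66 in total (33 per arm) if everyone is retained or imputed, and 46 in total (23 per arm) after the planned attrition.

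**2. The two analyses side by side.**

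| | GAD-7 | ISI and SF-36 |
|---|---|---|
| Normality check | each group and time cell | each time point |
| Effects tested | group, time, group x time | pre versus post |
| Between-arm test named | yes | no |
| Non-parametric fallback | none stated | Friedman, attached to normal scores |

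The group factor is absent from the secondary text twice: in the normality check and in the ANOVA. The text does not say whether the pre-post test pools the arms or is run within each arm, so both are worked out.

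**3. Chance of a significant pre-post result when the device does nothing.** Assumption, not in the protocol: both arms change equally by dz = 0.2 to 0.5, where dz is mean change divided by the SD of change. For two time points the test is a paired t-test with noncentrality dz x sqrt(n) and n - 1 degrees of freedom, two-sided 0.05. Example, n = 66 and dz = 0.2: 0.2 x sqrt(66) = 1.62 against a critical value of 2.00, probability 0.36.

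| dz | Pooled, n = 66 | Pooled, n = 46 | One arm, n = 33 | One arm, n = 23 |
|---|---|---|---|---|
| 0.2 | 36% | 26% | 20% | 15% |
| 0.4 | 89% | 76% | 61% | 45% |
| 0.5 | 98% | 91% | 80% | 63% |

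**4. The same situation with a between-arm test.** This was simulated with 10,000 trials per setting: 23 or 33 per arm, assumed pre-post correlation 0.5 or 0.7, common change 0 to 0.5 SD of the score, and no arm difference. The group x time test was significant in 4.3% to 5.6% of trials, whatever the common change. A pooled two-time-point Friedman test was significant in 20% to 99% of trials with a common change of 0.2 to 0.5 SD. It therefore has the same defect as the pre-post ANOVA.

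**5. What a null sham result can show.** The 95% interval for mean change within one arm has half-width t / sqrt(n) in SDs of change: 2.037 / sqrt(33) = 0.35, and 2.074 / sqrt(23) = 0.43. A non-significant result is compatible with real changes of roughly that size or more.

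**The case against.** Several counter-arguments deserve weight.

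- **The group factor may be implied.** The post hoc sentence mentions comparisons between groups without restricting them to GAD-7, and Cohen's d is promised for each outcome. But the post hoc sentence comes directly after the GAD-7 ANOVA and before any secondary outcome is mentioned, and d is not a test and is not said to be between arms. Neither fills the gap. A reader might still infer that the randomised comparison is abandoned for all secondary outcomes. The document supports less: no between-arm test is named.
- **The Friedman sentence is a slip.** Very likely so. A reader might call the rule inverted, or conclude that non-normal scores would go untested. In fact the condition is duplicated rather than swapped, and the intention is easy to guess. What stands is that the corrected sentence still gives a fallback without an arm comparison.
- **ISI.** Because entry requires "having an Insomnia Severity Index < 14", a reader might infer that ISI is the outcome most likely to fail the normality test. The limit truncates baseline only, and no distributional data are given, so there is no basis for ranking ISI above SF-36.
- **The percentages are not false-positive rates.** Correct. A pre-post test that detects a real common change is doing its job, and the table shows its power. The error would lie in attributing that change to the device. The size also depends on an assumed dz and on attrition, so no single figure, such as 89% at dz = 0.4, should be taken as the answer.
- **Only secondary outcomes are involved.** This stands and limits the severity.

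**Conclusion.** The point holds in this form: for ISI and SF-36 the protocol article names only a pre-versus-post test and a fallback that cannot compare arms, in a sham-controlled trial whose secondary hypotheses contrast the arms. That conclusion comes from the text and needs no numerical assumption.

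The size does rest on assumptions: equal change in both arms of dz 0.2 to 0.5, no device effect, two time points and two-sided 0.05. On these, the stated analysis gives a significant result in 26% to 98% of trials if pooled (46 to 66 people) and in 15% to 80% if run within one arm (23 to 33 people). With no common change, all the tests stay near 5%.

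GAD-7 keeps its between-arm test, and the stated sample size, alpha and power are unaffected. This should be fixed before the data are analysed, but it does not threaten the primary result.

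**What to change.** 1. Apply to ISI and to the SF-36 physical and mental component summaries the same group, time and group x time analysis already stated for GAD-7, and base conclusions on the between-arm contrast. A baseline-adjusted arm difference is an acceptable alternative, not a requirement.
2. Replace the Friedman sentence with a between-arm fallback for scores that are not normally distributed, for example a Wilcoxon rank-sum test on change from baseline.
3. Restate the sham no-change hypothesis as a difference between arms.

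These steps address the arm contrast only. The part of the secondary hypothesis about higher usage is a separate question, because the usage regression is planned for GAD-7 alone.

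The cost is a few sentences of analysis wording, with no extra data and no change in sample size.

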### 2.2. Subjects and Sample Size Estimation

Since the collaborative UK study is ongoing, we thus have to take reference of a similar CES study on GAD [23] on ‘Clinical effectiveness and cost minimization model of Alpha-Stim cranial electrotherapy stimulation in treatment seeking pts with moderate to severe GAD’. Participants in the CES group had a significant reduction in GAD-7 score (from baseline 15.77 (3.21) to 10.14 (4.86) (Cohen’s *d* = 1.3)) after 4 weeks of CES treatment.

Considering this trial is a sham-controlled trial, we hypothesize a large effect in the MS group. We used G*power version 3.1.9.7 (https://stats.oarc.ucla.edu/other/gpower/) (accessed on 1 April 2022) nto calculate the target sample size. With a statistical power of 99% and a statistical significance level at 0.05 to detect a large between-groups effect size of 1.3, each group will require 33 subjects. With an estimated attrition rate of 30% during the 12-week post-treatment follow-up, a total sample of 66 is required in this trial.

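### Section 3 plans a Cohen's d without a contrast, next to a pre-versus-post analysis, and section 2.2 labels a one-arm pre-to-post d as between-groups

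*Protocol article*

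**What the plan says.** Section 3 of the protocol article treats the two sets of outcomes differently.

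- **GAD-7 (primary).** A repeated-measures ANOVA tests group, time and "group x time interaction effects of the GAD-7 score between the VeNS group and the sham VeNS group". Bonferroni-corrected pairwise t-tests are then planned, some comparing the arms and some comparing visits, so both kinds of contrast are open at that step.
- **Insomnia and quality of life (secondary).** For normally distributed scores, "ANOVA with repeated measures will be used to determine whether the outcome scores are significantly different between pre-and post-test periods". The alternative is a Friedman test, which is also within-subject. No group term is named for these outcomes.

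The effect-size sentence follows directly: a Cohen's d "effect size for each outcome will be calculated, where d = 0.2, 0.5, and 0.8, corresponding to small, medium, and large effect sizes". It names no contrast, visit or standardising SD.

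Section 2.2 gives the only d that the document works with. The cited cranial electrotherapy study is summarised by its treated arm alone, "from baseline 15.77 (3.21) to 10.14 (4.86", with a Cohen's d of 1.3 at 4 weeks. The next paragraph powers the trial "to detect a large between-groups effect size of 1.3".

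Section 1.2.1 expects GAD-7 to fall by at least 50% in the active arm and by less than 5% under sham. Section 1.2.2 expects no change under sham in insomnia or quality of life.

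**The concern.** In a sham-controlled trial, the effect of the device is what the active arm gains over sham. A pre-to-post d in the active arm also contains regression to the mean after entry on a high GAD-7 score, the passage of time, and any response to a sham built to feel active (section 2.8.2). If the sham response is not negligible, that d exceeds the device effect, and readers quote the effect size.

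Two things in the text point towards the pre-to-post reading. The analysis nearest to the d sentence is pre versus post, and section 2.2 has already treated a pre-to-post d as a between-groups one. An analyst who follows the text for insomnia and quality of life could reasonably report a within-arm d under the heading of the VeNS effect.

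**Working it through.** **Inputs.** From section 2.2: cited treated-arm mean 15.77 (SD 3.21) at baseline and 10.14 (SD 4.86) at 4 weeks; d = 1.3; 99% power; significance level 0.05; 30% attrition; 33 per group. From section 1.2.1: sham fall below 5%. Assumed: a two-sided test, equal baseline means and the same SDs in both arms, and sham falls of 2 and 4 points as illustrations.

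**Step 1: the stated sample size.** A two-sample t-test with d = 1.3, two-sided 0.05 and 99% power needs 23 per group. Allowing for attrition, 23/(1 − 0.30) = 32.9, so 33 per group and 66 in total. The figure reproduces, so 1.3 was entered as a between-groups d.

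**Step 2: what the 1.3 is.** The change is 15.77 − 10.14 = 5.63 points.
- On the 4-week SD: 5.63/4.86 = 1.16.
- On the average SD, √((3.21² + 4.86²)/2) = 4.118: 5.63/4.118 = 1.37.
- On the baseline SD: 5.63/3.21 = 1.75.

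The stated 1.3 lies in this range. All three values are changes in one arm, and no control arm enters any of them.

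**Step 3: the same active-arm change under the two contrasts.** Between-arm d = (5.63 − sham fall)/SD. The protocol's 5% limit on the cited baseline is 0.05 × 15.77 = 0.79 points.

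| Sham fall (points) | Active minus sham | d, average SD 4.118 | d, 4-week SD 4.86 | d, baseline SD 3.21 |
|---|---|---|---|---|
| 0 | 5.63 | 1.37 | 1.16 | 1.75 |
| 0.79 (protocol's limit) | 4.84 | 1.18 | 1.00 | 1.51 |
| 2 (assumed) | 3.63 | 0.88 | 0.75 | 1.13 |
| 4 (assumed) | 1.63 | 0.40 | 0.34 | 0.51 |

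The pre-to-post d in the active arm stays in the first row whatever sham does. On the average SD it overstates the between-arm d by 0.19 at the protocol's own sham limit, and by 0.97 if sham falls 4 points.

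**Step 4: the standardiser matters too.** With a 4-point sham fall, d runs from 0.34 to 0.51 with the choice of SD alone. A d can therefore be reproduced only if its SD is named as well as its contrast.

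These are GAD-7 figures. The document gives no comparable numbers for the Insomnia Severity Index or SF-36, so the size of the problem there is shown by analogy only.

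**The case against.** The strongest reply is that much of this is omission. Section 3 nowhere says that d will be pre-to-post, and an article may leave the SD, the visit and the interval to a fuller document that is not shown. That stands for the missing interval and formula, which alone would be no finding. It does not dispose of the contrast, because the adjacent secondary analysis is stated as pre versus post and section 2.2 shows the two kinds of d being interchanged.

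A second reply is that, if sham behaves as sections 1.2.1 and 1.2.2 expect, the two readings nearly agree (1.18 against 1.37). That is correct arithmetic. But the sham response is what the control arm is there to measure, so the reported effect should not presume it.

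A reader might also infer more than the document supports:

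- **That section 2.2 names no contrast.** It does: "detect a large between-groups effect size of 1.3, each group will require 33 subjects". Its fault is that a within-arm value carries that label.
- **That the primary test is compromised.** It is not, because the group-by-time test compares the arms and between-group post hoc tests are planned. A null or modest GAD-7 result would remain interpretable.
- **That the small, medium and large grades will mislead.** The plan lists them as benchmarks and ties no conclusion to them. For a true between-arm d of 0.65, the point estimate would fall in the wrong band in about 55% of trials with 33 per arm and 62% with 23. At the planned 1.3 this is only 2.5% to 5%. Sampling error of this kind is a caution for true effects of about 0.2 to 0.8, and is not part of the point.

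**Conclusion.** The point holds for the reported effect sizes. Section 3 does not fix the contrast for d, and for insomnia and quality of life the only analysis described beside it is within-subject. The d for GAD-7 is open as well, though its test is not. Section 2.2 presents a one-arm pre-to-post d as a between-groups effect.

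On the cited GAD-7 figures and the average SD, a pre-to-post d of 1.37 corresponds to a between-arm d of 1.18 at the protocol's 5% sham limit, 0.88 at a 2-point sham fall and 0.40 at a 4-point fall. The last two rest on assumed sham responses, and all rest on equal baseline means and SDs in the two arms. The document does not show that a pre-to-post d will be reported, only that its wording allows one and leans that way. The change is worth making because it costs almost nothing.

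**What to change.** In section 3, state that the reported effect for each outcome is the active-minus-sham difference in change from baseline at each post-baseline visit, in scale points with a 95% confidence interval. If d is also given, base it on that same contrast, with one SD named in advance and a 95% confidence interval. Choose that SD with the entry limits in mind: GAD-7 above 10 and Insomnia Severity Index below 14 may narrow the baseline spread, and a smaller SD gives a larger d. Label any within-arm d as descriptive.

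In section 2.2, state that the 1.3 is a within-arm pre-to-post value from the cited study, adopted as a planning assumption, and not an observed between-groups effect.

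The cost is wording only, with no new data or visits. The reported effects may look less favourable than a pre-to-post d would.

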## Abstract

The prevalence of symptoms of anxiety is increasing, especially during the COVID-19 pandemic. A home use transdermal neurostimulation device might help to minimize the severity of anxiety disorder. To the best of our knowledge, there is no clinical trial using transdermal neurostimulation to treat individuals with symptoms of anxiety in Asia. This gives us the impetus to execute the first study which aims at evaluating the efficacy of Electrical Vestibular Stimulation (VeNS) on anxiety in Hong Kong. This study proposes a two-armed, double-blinded, randomized, sham-controlled trial including the active VeNS and sham VeNS group. Both groups will be measured at baseline (T1), immediately after the intervention (T2), and at the 1-month (T3) and 3-month follow-up (T4). A total of 66 community-dwelling adults aged 18 to 60 with anxiety symptoms will be recruited in this study. All subjects will be computer randomised into either the active VeNS group or the sham VeNS group in a 1:1 ratio. All subjects in each group will receive twenty 30 min VeNS sessions during weekdays, which will be completed in a 4-week period. Baseline measurements and post-VeNS evaluation of the psychological outcomes (i.e., anxiety, insomnia, and quality of life) will also be conducted on all participants. The 1-month and 3-month follow-up period will be used to assess the long-term sustainability of the VeNS intervention. For statistical analysis, ANOVA with repeated measures will be used to analyze data. Missing data were managed with multiple mutations. The level of significance will be set to *p* < 0.05. Results of this study will be used to determine whether this VeNS device can be considered as a self-help technological device to reduce perceived anxiety in the general population in the community setting. This clinical Trial was registered with the Clinical Trial government, identifier: NCT04999709.

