### 1.2. Hypotheses

#### 1.2.1. Primary Hypothesis

Participants in the active VeNS group will have at least a 50% reduction in their (General Anxiety Disorder-7) (GAD-7) score after four weeks of treatment, and this will be maintained for the 12-week follow-up. However, participants in the sham VeNS group will have a <5% reduction in their GAD-7 score after the 4-week treatment and during the 12-week follow-up.

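### The missing-data rule equates multiple imputation with LOCF; if LOCF is what is run, the 3-month maintenance claim is partly assumed

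*Protocol article*

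**What the plan says.** Section 3 (Statistical Analyses) of the protocol article ends with the rule: "Missing data will be managed with multiple imputation [36] by adopting the last observation carried forward (LOCF) method". The abstract has "Missing data were managed with multiple mutations", evidently a slip for imputations, and does not mention LOCF.

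Three other places determine what the rule does:

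- Section 1.2.1 expects a GAD-7 reduction of at least 50% in the active arm "after four weeks of treatment, and this will be maintained for the 12-week follow-up", while "participants in the sham VeNS group will have a <5% reduction in their GAD-7 score".
- Section 2.2 places the expected losses in follow-up: "With an estimated attrition rate of 30% during the 12-week post-treatment follow-up, a total sample of 66 is required in this trial".
- The abstract lists four visits: baseline (T1), end of treatment (T2), 1 month (T3) and 3 months (T4). Section 2.1 lists T1, T2 and T4 only.

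The primary analysis is a repeated-measures ANOVA with a group by time interaction. It is followed by Bonferroni-corrected post hoc t-tests between groups and time points.

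**The concern.** Multiple imputation draws several plausible values for each missing score and carries the spread between draws into the standard error. LOCF is deterministic: it copies the last score. Copying it m times gives m identical data sets, so Rubin's rules have nothing to add. The sentence therefore names two different analyses as one, and an analyst could run either and claim to have followed the plan.

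The choice matters because of where the losses fall. If they fall between T2 and T4, LOCF credits those participants with an unchanged end-of-treatment score. Maintenance over that interval is what the second half of the primary hypothesis asserts, so for the missing share of the sample the claim is assumed and not tested. The filled-in scores are also counted as observed data.

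**Working it through.** **1. The plan's own figure.** A two-sided two-sample t-test with d = 1.3, alpha 0.05 and power 99% needs 23 per group (power 0.9906). Allowing for 30% attrition, 23 / 0.70 = 32.9, so 33 per group and 66 in total, as stated. The plan thus expects about 0.30 × 33 ≈ 10 missing T4 scores per arm.

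**2. Bias formula.** Let p be the share lost after T2, equal in both arms and at random, and let D2 and D4 be the true arm differences at T2 and T4. Under LOCF:

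- expected T4 difference = (1 − p) × D4 + p × D2
- bias = p × (D2 − D4)

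If both arms lose a share r of their improvement by T4, then D4 = (1 − r) × D2 and the bias is p × r × D2.

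**3. Inputs.** p = 0.30 (section 2.2). The baseline of 15.77 is the reference study's (section 2.2).

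- Hypothesised reductions (section 1.2.1, taken at 50% and 5%): D2 = 15.77 × (0.50 − 0.05) = 7.10.
- Reference study's active-arm change with 5% in sham: (15.77 − 10.14) − 0.05 × 15.77 = 5.63 − 0.79 = 4.84.

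The relapse share r is not in the documents, so a range is shown.

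| Relapse by T4 | Bias, D2 = 7.10 | Bias, D2 = 4.84 |
|---|---|---|
| 0% | 0 | 0 |
| 25% | 0.53 | 0.36 |
| 50% | 1.06 | 0.73 |
| 75% | 1.60 | 1.09 |
| 100% | 2.13 | 1.45 |

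**4. Unequal loss.** At full relapse with D2 = 7.10, loss of 30% active and 10% sham gives 2.29 points. Loss of 10% active and 30% sham gives 0.55.

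**5. If T3 is held.** Suppose half of the losses come after T3 and half of the effect has gone by then (both assumed). At full relapse the bias is 0.15 × 7.10 + 0.15 × 3.55 = 1.60 points instead of 2.13.

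**6. Standard error with no relapse.** In simulation (33 per arm, SD 4.86 at T2 and T4, correlation 0.5 assumed) the mean SE was 1.19 under LOCF and 1.44 under multiple imputation by arm with Rubin's rules. Full data would give √(2 × 4.86² / 33) = 1.20. LOCF therefore reports the precision of a trial with no missing T4 scores. The gain comes from the no-change assumption, so the SE is too small unless maintenance is taken for granted.

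**7. Rejection at T4 when the true difference is zero.** This is full relapse, the worst case, with the same simulation settings and a two-sample t-test at T4.

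| | D2 = 4.84 | D2 = 7.10 |
|---|---|---|
| Unadjusted 0.05 | about 20 to 21% | about 33 to 35% |
| Bonferroni, 3 or 4 comparisons (nominal 1.7% or 1.25%) | about 8 to 10% | about 16 to 19% |

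The number of comparisons is an assumption. Multiple imputation in the 7.10 case had mean bias 0.00 and rejected 4.4% of the time at an unadjusted 0.05.

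**The case against.** The sentence is ambiguous. Read past its misprint, the abstract names only multiple imputation, and the citation in section 3 is attached to that term. If genuine multiple imputation is run, none of the LOCF bias arises. This stands: the contradiction is certain, and the bias is conditional on the LOCF reading.

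A reader might infer that the trial's primary test has a false-positive rate of about one in three. The documents do not support that. The primary test is the group by time interaction, and with a large T2 difference that vanishes by T4 a true interaction exists, so rejecting it is no error. Only the post hoc T4 contrast is affected. Section 3 applies Bonferroni to such contrasts, which lowers the rate, though it stays well above the adjusted nominal level. Full relapse is also the extreme of a range on which the documents are silent.

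A reader might also infer that LOCF must favour the active device. That is not so in general. With no relapse the mean is unbiased. A T3 visit would reduce the carry-over. Anyone lost before T2 would carry the baseline score, which pulls towards no difference, although the plan gives no figure for such losses.

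Finally, an analysis plan that is not shown might add detail. That does not rescue a rule that the protocol itself states in contradictory form.

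**Conclusion.** Wrong as written. The methods fix a missing-data rule that cannot be carried out as worded, and nothing elsewhere in the document corrects it.

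If LOCF is the part that is implemented, the T4 GAD-7 difference is biased towards the T2 difference. The size is about 0.5 to 2.1 points on the hypothesised reductions and 0.4 to 1.5 points on the reference study's change, for relapse of 25% to 100%. This assumes 30% random loss in each arm, all after T2, and a baseline of 15.77. The rejection rates rest further on SD 4.86, correlation 0.5 and full relapse, and show only how bad the T4 contrast could become.

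The T2 comparison, the first half of the primary hypothesis, is untouched if losses follow T2. The damage is confined to the maintenance claim.

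**What to change.** In section 3, delete LOCF as the primary method and name one coherent method:

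- a likelihood-based mixed model for repeated measures on all observed visits of all randomised participants, which would take the place of the repeated-measures ANOVA; or
- genuine multiple imputation by arm using the observed visits, pooled with Rubin's rules, if the ANOVA is to be kept.

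Keep LOCF at most as a labelled sensitivity analysis. Correct the abstract so that it names the same method.

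The cost is a change of wording and a little analysis code. No new data are needed and the sample size stays at 66. Intervals at T4 become somewhat wider (SE about 1.44 instead of 1.19 under the assumptions above).
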